These therapeutic uncertainties contribute to patients' treatment dissatisfaction. Relatively high percentages of headache sufferers are not satisfied with the headache care they receive. Harpole and co-workers investigated the headache burden and patient satisfaction with existing management in primary care, using patient-administered surveys. Of the 385 responders, who all contacted a GP because of their headache, 48 % reported problems with headache management and 17 % were dissatisfied with the headache care. Patients with a high headache-related impairment reported more problems with their headache management [20]. Walling et al. found that 26 % were dissatisfied in their sample of 447 migraine patients [21].

The prevalence and burden of headache, the dissatisfaction percentages and the diversity in headache treatments, call for a refinement of headache management.

The identification prior to the start of a treatment, of patients whom might react properly to the treatment, is necessary to reduce the risk of a negative outcome. For this purpose, patient characteristics which predict the treatment outcome (prognostic characteristics) need to be determined.

Prognostic factors are multifactorial. Jull and Stanton analysed the results of 152 CErvicogenic Headache (CEH) patients who participated in one of the three active treatment groups in a headache trial [9]. The prognostic value of socio-demographic factors, headache features, physical impairments of the cervical spine, neck pain and disability and patients' perceptions of influences on their headaches (locus of control) was investigated. They were unable to identify a systematic pattern of prognostic factors. Only the presence of light-headedness appeared to be a clinically relevant predictor of a bad outcome. Of the physical tests only joint pain on palpation had a prognostic value [22]. Of their tests only this palpation could be used for prognostic uses.

Our study has a double aim. Our primary aim is to analyse the prognostic value of a series of physical tests. Our secondary aim is to compare two currently applied treatment strategies, being the usual care (UC) administered by a medical doctor following a stepped guideline [7], and the UC plus a musculoskeletal physiotherapy treatment protocol (UCMT), described by Jull et al [9].

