### Follow-up measurements

After approximately 7, 12, 26 and 52 weeks, participants will be asked to complete the Headache Inventory List and HIT-6 again. For all questionnaires a recall period of four weeks is chosen, in correspondence with the recall period of the HIT-6.

The global perceived effect (GPE) is measured using a 7 point scale, ranging from 'completely recovered' to 'worse than ever'. This way of measuring GPE has been used in similar studies in which the effect of commonly applied therapeutic approaches have been compared [37,38]. Responders (positive effect) and non-responders (no effect or worse) can be identified.

The follow-up measurements are also available online ensuring a blinded rater assessment. The questionnaires which are returned in paper version (from participants without internet connection) will be inserted in the software by an independent blinded rater.

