#### Primary and secondary outcome measures

Two primary outcome measures will be used in this study: GPE and the HIT-6 score.

Reduction in headache frequency, headache pain intensity, medication intake, absenteeism and looking for professional help will be used as secondary outcome measures.

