### Statistical analyses, power and sample size calculation

The prognostic capacity of the initial series of tests (physical examination of the cervical spine and QST) will be calculated by means of a logistic regression analysis, comparing the results of the responders with those of the non-responders. Instead of starting with a full regression model, two known prognostic factors, derived from the study from Jull and Stanton [8] will be included in the analysis a priori. Those two factors are 'light-headedness' and 'joint pain on palpation'. Consequently a backwards stepwise selection will be used, including the two known factors in the smaller models. Differences at baseline between the two treatment groups will be included in the regression models as potential prognostic factors. The plausibility of the signs will be considered to check the logical contribution of each factor in the model. The power of the obtained models will be analysed via the area under the ROC-curve.

Group differences and effect sizes can be calculated for headache intensity and frequency, medication intake, HIT-6 scores and absenteeism. The number of responders and non-responders in both groups will be compared. GPE is a dichotomous variable. Sample size calculations with a significance level of p < 0.05, an event rate of 0.50 in the usual care group and of 0.70 in the usual care plus musculoskeletal physiotherapy group a power of 80% and an equal amount of subjects in both treatment groups result in a sample size of 93 subjects in each treatment group. This results in a total of 186 subjects.

The results of all subjects will be analysed, regardless of their treatment adherence (intention-to-treat analysis).

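### HIT-6 is declared a primary outcome, but the analysis of the primary (prognostic) aim uses only dichotomised GPE

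*Protocol article*

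**What the plan says.** All places are in the Protocol article.

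- **Outcomes** (Primary and secondary outcome measures): "Two primary outcome measures will be used in this study: GPE and the HIT-6 score". No order is given. The secondary outcomes are listed separately, without HIT-6: "Reduction in headache frequency, headache pain intensity, medication intake, absenteeism and looking for professional help will be used as secondary outcome measures".
- **Aims** (Background): "Our primary aim is to analyse the prognostic value of a series of physical tests"; then "Our secondary aim is to compare two currently applied treatment strategies". The Discussion repeats that prognosis comes first.
- **Prognostic analysis** (Statistical analyses, power and sample size calculation): the prognostic capacity of the tests "will be calculated by means of a logistic regression analysis, comparing the results of the responders with those of the non-responders".
- **Responder status** (Follow-up measurements): it comes from the 7-point GPE rating, split in two: "Responders (positive effect) and non-responders (no effect or worse) can be identified". The Abstract agrees.
- **HIT-6 in the statistics section**: one mention, "Group differences and effect sizes can be calculated for headache intensity and frequency, medication intake, HIT-6 scores and absenteeism".
- **HIT-6 as a measure**: its own section gives a range of 36 to 78 and an important difference of three points. It is taken at baseline and at about 7, 12, 26 and 52 weeks.

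**The concern.** The outcome section and the statistics section give HIT-6 different standing. In the first it ranks equally with GPE. In the second it has no part in the primary aim and sits in a list whose other four members are all secondary outcomes.

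What is at stake is the prognostic conclusion, which would rest on a yes/no split of one patient rating. The planned checks on the model, plausibility of signs and area under the ROC curve, concern that same split. A physical test related to later headache burden but not to the GPE split would not be selected. A test related only to the GPE split would be accepted without being looked at on the other primary outcome. The data for that second look are already being collected.

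**Working it through.** **1. The passages side by side**

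| | GPE | HIT-6 |
|---|---|---|
| Declared status | primary | primary |
| Prognostic model (primary aim) | logistic regression, committed | none |
| Arm comparison (secondary aim) | responder counts, committed | group difference and effect size, 'can be' calculated |
| Basis of the sample size | yes | no |

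The gap lies in what the article states: its statistics section fixes the outcome of the prognostic model, and that outcome is GPE alone.

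**2. The plan's own figure**

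Inputs from the statistics section: event rates 0.50 and 0.70, alpha 0.05 (taken as two-sided), power 80%, equal groups. The pooled-variance formula without continuity correction is

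n = [1.960·√(2·0.60·0.40) + 0.842·√(0.50·0.50 + 0.70·0.30)]² / 0.20²
= [1.358 + 0.571]² / 0.04 ≈ 93 per group, 186 in total.

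This matches. It supports the arm comparison on GPE, which is the secondary aim.

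**3. What a binary split costs, as an illustration**

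Assumptions, not in the article: a normal latent outcome behind the split; one normally distributed predictor with correlation r to it; 60% responders overall, (0.50 + 0.70)/2; a two-sided 5% test; N = 186.

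- Expected non-responders: 93·0.50 + 93·0.30 = 46.5 + 27.9 ≈ 74.
- Attenuation of r: φ(z₀.₆)/√(0.6·0.4) = 0.386/0.490 = 0.789.
- Relative efficiency: 0.789² = 0.62, so 186 patients inform like 186·0.62 ≈ 116.
- Power: Φ(atanh(r)·√183 − 1.96), with r replaced by 0.789·r for the split outcome.

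| r | Continuous outcome | Split outcome |
|---|---|---|
| 0.15 | 53% | 36% |
| 0.20 | 78% | 58% |
| 0.25 | 93% | 77% |
| 0.30 | 99% | 90% |

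**4. How far this carries over to HIT-6**

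Read as HIT-6 against GPE, the table requires a test to correlate equally with HIT-6 and with latent GPE. If the correlation is 0.25 with latent GPE and 0.20 with HIT-6, power is 77% (split GPE) against 78% (HIT-6). At 0.20 and 0.15 it is 58% against 53%. A difference of 0.05 therefore removes the advantage. The article gives no correlations and no HIT-6 standard deviation, so the gain for this trial cannot be computed.

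**The case against.** **An outcome can be primary for one aim only.** The article has two aims and does not say that both primary outcomes must serve the prognostic one. The Abstract, Follow-up measurements and the statistics section consistently tie prognosis to GPE responders. A binary outcome also suits a referral tool judged by ROC area. This stands as a defence of using GPE responders, and the logistic model should stay. It does not explain why the other primary outcome has no role in the primary aim and, under the secondary aim, is placed among secondary outcomes.

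**'Can be' may be only a turn of phrase.** The article uses it for a step it depends on, the identification of responders: "Responders (positive effect) and non-responders (no effect or worse) can be identified". This also stands: the wording alone does not show that the HIT-6 comparison is optional. The point rests on the absent prognostic role and on the company HIT-6 keeps in the list.

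**Modelling detail belongs in a fuller document.** True of covariates and time points. But the article itself states which outcome the prognostic model uses.

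**A reader might infer that the plan has been shown to lose power.** The documents do not support that. The comparison in step 4 of the working depends on equal correlations that nothing in the article supports. It also assumes a single normal predictor, whereas the cervical tests are scored positive or negative and the plan is a multivariable backward selection with two forced factors.

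**A reader might also want to call a test prognostic only if its direction agrees on both outcomes.** That adds a hurdle and recovers no information. It is also ill defined when backward selection keeps different tests in the two models.

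**Conclusion.** The point holds as an inconsistency between declared outcomes and planned analysis. The primary aim is answered on one of the two declared primary outcomes. The other, a continuous score with a baseline value and a stated important difference, is unused for it. This rests on the text alone and needs no assumption.

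The statistical consequence is plausible but not quantified for this trial. The 62% figure describes splitting a normal latent outcome at 60% responders; it is not the gain from adding HIT-6, which is a different measure. No stated figure is wrong: 93 per group at 80% power is correct for the comparison it was made for. Nor is the choice of GPE responders itself a fault.

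**What to change.** In the statistics section:

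1. Keep the logistic model for GPE responders.
2. Add a committed linear prognostic model with follow-up HIT-6 as outcome and baseline HIT-6 as covariate. Use the same two forced factors (light-headedness and joint pain on palpation), the same candidate tests and the same follow-up time point as the GPE model. Report both sets of results, with no rule that they must agree.
3. State that the HIT-6 comparison between arms will be made, adjusted for baseline HIT-6, and separate it from the secondary outcomes.

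If the authors do not want a HIT-6 prognostic model, they should name HIT-6 as secondary in Primary and secondary outcome measures.

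The first route costs one extra regression on data already collected. Its drawback is two sets of prognostic results, which may disagree and would both have to be reported. The second route costs one sentence. Neither changes the sample size.

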## Discussion

This study aims to improve the care for headache patients. Therefore we compare two commonly applied therapeutic strategies: the usual care, administered by the GP, and usual care plus musculoskeletal physiotherapy treatment. We primarily want to screen for prognostic patient characteristics.

For the selection of patients we start from the clinical presentation of symptoms: we look for patients with a combination of headache and neck pain. We not only focus on CEH, but allow migraine and tension-type headache patients to be included as well. We believe this is justified because of the common combination of symptoms.

Is it ethical to provide musculoskeletal physiotherapy treatment to patients with migraine symptoms? Several systematic reviews have been performed concerning the value of physical treatments directed to the cervical spine in headache disorders such as migraine [10,11,39]. These reviews were unable to draw firm conclusions due to the methodological quality of the included RCTs. However, there are indications that physical treatments can be beneficial. There is no group that receives only musculoskeletal physiotherapy treatment. The combination with the GP care is allowed at all times. Prohibiting the use of medication, certainly during a headache attack, would be unethical.

We use a diagnostic headache questionnaire. The value of diagnostic questionnaires in comparison with a clinical interview has been studied [40]. Questionnaires have their limitations [40]. They lack the flexibility of a clinical interview, in which questions can be repeated or reformulated whenever a patient does not fully understand their meaning. Then again the phrasing of a questionnaire is more standardised which we consider as preferential. Rasmussen et al. also mention methodological pitfalls. They particularly mention the internal consistency and test-retest repeatability. Reliability scores of our questionnaire are very high (kappa: 0.982, sign.: <0.001), as well as the internal consistency (Cronbach alpha: 0.87) [30]. Considering these methodological aspects we believe that the use of this questionnaire is justified.

We preferred not to include generic questionnaires like the SF-36 in our outcome measures. This was mostly out of practical considerations: the initial set of questionnaires is quite long to complete. Adding another questionnaire can discourage patients to participate. The influence of migraine, tension-type headache and CEH on Quality Of Life (QOL) has been investigated before [41].

Quantitative Sensory Testing using thermal and pressure stimuli have been used to study patho-physiological mechanisms in headache patients [42-46]. General hypersensitivity has been demonstrated to be present in Whiplash patients with moderate to severe symptoms and not in recovered patients or those with mild symptoms [47]. This indicates the potential value of this test in predicting the evolution of a disorder.

The number of participants is the weak point of every clinical study. A pilot running from February 06 to June 06, with only first line recruitments resulted in 15 referred patients. To obtain the required number of patients the way of recruitment was adapted. Second line and advertisement recruitments were also included. The results will be analysed as in any multicenter trial: intercenter differences will be analysed to verify if patients can be pooled.

No training sessions dealing with the study protocol or treatments were organised for the participating medical doctors or therapists. This is a potential weakness of the study protocol. It was impossible to organize these sessions. The referring doctors receive no financial incentives or compensations whatsoever for participation in this study. They participate out of goodwill. Additional time investments would decrease this goodwill. We tried to have their commitment by informing them personally and by providing additional information on a website developed for that purpose [23].

The therapists could not be trained in advance either as it is not known in advance which therapists will participate. This depends on the patient's residence. Therefore the letter with treatment recommendations is provided.

The treatment part of the study protocol is a potential barrier for doctors to participate in the study. Clinicians have treatment preferences. Study protocols require a step back from daily routine, and maybe ask to prescribe a treatment one does not fully support. This can influence the selection of patients: one can refer only those patients who do not fit in the regular schema or where the regular schema was not successful. To anticipate this phenomenon, we contacted all doctors personally, informed them about the study protocol and asked them to collaborate. We labelled one of the treatment groups as the usual care group to link the study protocol with every day practice explicitly.

Patients who are willing to participate are informed prior to the study (written informed consent). Patients with a preference for one of the treatment groups are potentially biased when included.

For these reasons Pfeiffer et al. decided to use a prospective cohort study rather than a randomised controlled trial [48]. In case a study protocol acquires a too low number of patients, using a non-randomised protocol can be an option.

With this study we hope to detect variables that can predict the outcome of the treatment of headache patients, and that consequently can help to improve the care for these patients.

## List of abbreviations

HIT-6: Headache Impact Tests, 6 items

UC: Usual Care

UCMT: Usual Care plus Musculoskeletal Physiotherapy Treatment

GP: General Practitioner

RCT: Randomised Clinical Trial

CEH: CErvicogenic Headache

IHS: International Headache Society

CHISG: Cervicogenic Headache International Study Group

VAS: Visual Analogue Scale

QST: Quantitative Sensory Testing.

CS: Cold Sensation

WS: Warm Sensation

CP: Cold Pain

HP: Heat Pain

GPE: Global Perceived Effect

QOL: Quality Of Life

SF-8: Short form-8 quality of life questionnaire

SF-36: Short form-36 quality of life questionnaire
